**Conclusion:**

The intervention group is expected to demonstrate significantly lower scores
in psychological distress during both the immediate evaluation and the
assessment conducted three months post-intervention, compared to the
wait-list group. Additionally, the intervention group is anticipated to
exhibit enhanced levels of HIV prevention practices and coping
self-efficacy, resulting in a greater degree of adjustment.

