## Methods

This quasi-experimental study follows a non-randomized controlled trial design, in
which participants are assigned to either the intervention group, receiving the
mobile health KaPi program, and the control group, receiving standard educational
materials in the form of e-books. To minimize potential bias, participants will be
blinded to their group allocation; they will not be informed whether they are
receiving the intervention or serving as part of the control group. Efforts will be
made to ensure that the delivery of content appears comparable across groups to
prevent participants from discerning their allocation. Data collection took three
months from the first intervention given. To ensure that the intervention carried
out is in accordance with the standards, the researcher using the Standard Protocol
Items as a guide. The study will adhere to the Standard Protocol Items:
Recommendations for Interventional Trials (SPIRIT) guidelines ( Chan et al., 2016), the Consolidated Standards
of Reporting Trials (CONSORT) criteria ( Schulz et al., 2010), and the recommendations set forth by the Consolidated
Standards of Reporting Trials of Electronic and Mobile Health Applications and
Online Telehealth (CONSORT-EHEALTH) ( Eysenbach et al., 2011). Participation in the study was voluntary, and no financial
compensation was offered. To ensure the accuracy and validity of this study, we will
take strategic steps to minimize bias. The study will start with clear, testable
objectives and hypotheses, and random sampling will be used to ensure
representativeness. Data will be collected using valid, reliable instruments and
standardized procedures. A blind or double-blind design will be implemented to
reduce bias from both researchers and participants. Data analysis will follow
appropriate statistical methods to avoid misinterpretation. The research process
will be transparently reported, with methods and results available for replication.
Peer review and potential replication by other researchers will further confirm the
findings, ensuring the study produces valid, unbiased results.

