### Study design

This study will employ a quasi-experimental, non-randomized controlled trial
design with single blinding applied to participants. The control group will
receive standard therapy, while the intervention group will receive the mobile
health program. A parallel assignment approach will be used, reflecting the
structure of health services research. This study corresponds to a Phase
2–3 trial, aiming to evaluate both the feasibility and preliminary
effectiveness of the intervention. One or two (experimental group) receives the
Mobile health KaPi Program intervention under test and the other (comparison
group or control) receives the standard e book/leaflet. Then follow up on the
two or more groups to see if there are any differences in the results. The
results of the study and subsequent analysis are used to assess the
effectiveness of the intervention mobile health application. Quasi-experimental
are the most rigorous way to determine if there is a causal link between
interventions and outcomes ( Polit and Beck, 2017).  Figure 1 provides an
overview of the study design. The choice of this experimental design is grounded
in its robustness and efficacy ( Creswell, 2016).

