### Statistical analysis

Demographic characteristics and predictor variables were summarized as
frequencies (n) and percentages (%) for categorical data, and means with
standard deviations for continuous data. Descriptive statistics, including
percentage and frequency distributions, are presented using tables and charts.
Chi-square tests and independent t-tests (or ANOVA where appropriate) were used
to compare socioeconomic and baseline characteristics between the two study
groups.

For inferential analysis, the association between each independent variable and
the outcome variable was initially examined using binary logistic regression.
The primary outcomes—psychological distress (K10), HIV prevention
knowledge and practices (KAP VCT), and communication self-efficacy
(CSE)—were analyzed using Generalized Estimating Equations (GEE) to
account for repeated measures and within-subject correlations over time. The GEE
model included main effects of group and time, as well as their interaction term
(group × time), to evaluate differential changes between intervention and
control groups across three measurement points (baseline, post-intervention, and
4-week follow-up). Adjusted odds ratios with 95% confidence intervals are
reported.

Missing data will be handled under the missing at random (MAR) assumption
inherent in GEE, and sensitivity analyses will be conducted to assess the
robustness of findings.

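### The abstract expects an effect three months post-intervention against a wait-list, but the planned model stops at a 4-week follow-up and the control group receives an e-book

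*Protocol article*

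**What the plan says.** **Follow-up time.** The abstract's Conclusion names two assessments for psychological distress: an immediate one and an "assessment conducted three months post-intervention, compared to the" control group. The Statistical analysis section sets the time factor of the GEE at "three measurement points (baseline, post-intervention, and 4-week follow-up", and evaluates the intervention through the group × time interaction over those points. Two other places mention three months. The opening of the Methods says that data collection takes three "months from the first intervention given", and the Recruitment section gives three months as the study period over which participants are to be retained.

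**Comparator.** The abstract's Conclusion calls it a "wait-list group. Additionally, the intervention group is anticipated to" do better on HIV prevention practices and coping. The opening of the Methods describes two groups, one using the "mobile health KaPi program, and the control group, receiving standard educational" "materials in the form of e-books". The Study design section says that controls "receive standard therapy, while the intervention group will receive the mobile" health program, and later in the same paragraph that they get an e-book or leaflet. The wait-list appears only in the abstract, and no section says that controls receive the app later.

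**The concern.** A group × time model answers a question about particular times against a particular comparator. Here the article's statement of the expected result and its description of the model disagree on the later time, and the abstract and Methods disagree on the comparator.

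Three things are at stake.

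- **Durability.** A model whose last visit is at 4 weeks cannot support or refute an expectation about three months after the intervention.
- **Pre-specification.** Two candidate times for the later assessment, with neither named as primary, leave room to settle on one once results are known. The trial is not randomized, so a contrast fixed in advance matters all the more.
- **Interpretation.** The e-book covers mental health, coping and HIV. A difference from that material is the added effect of the app over written education. A difference from a wait-list is the effect over deferred help. Reporting the first as the second would mislead.

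**Working it through.** The check is mainly a comparison of text, with a little arithmetic on timing.

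**1. Assessments side by side.**

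| Source | Immediate | Later | Comparator |
|---|---|---|---|
| Abstract, Conclusion | yes | three months post-intervention | wait-list |
| Statistical analysis | yes | 4-week follow-up | control groups, not described |
| Methods, opening | – | three months of data collection, counted from first intervention | e-books |
| Study design | – | – | standard therapy; also e-book/leaflet |
| Recruitment | – | three-month study period | – |

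The immediate column agrees. The later and comparator columns do not.

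**2. Size of the time gap.** Three months is 3 × 52/12 = 13 weeks, and 13/4 = 3.25, so the two follow-ups differ about threefold. The K10 asks about the past four weeks. If both times are counted from the end of the intervention, a 4-week visit describes weeks 0 to 4 and a 13-week visit describes weeks 9 to 13. These periods do not overlap.

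**3. Does the three-month window reconcile the two?** Let D be the weeks from first to last session. A 4-week follow-up ends at D + 4, which fits 13 weeks if D ≤ 9. A visit three months after the intervention ends at D + 13, which fits only if D is close to 0. The program is 11 sessions of about 12 minutes, 11 × 12 = 132 minutes or 2.2 hours, and the article gives no spacing, so D is unknown. The window fits a 4-week follow-up easily. It fits the abstract's visit only if delivery is very short. In either case the window is an overall duration and not a stated visit three months after the intervention.

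**4. Does the sample size show how many visits are planned?** The stated inputs are a repeated-measures within-between interaction, 2 groups, f = 0.20, α = 0.05 and power 0.95, giving N = 66. The formulas are λ = f²·N·m/(1 − ρ), df1 = m − 1 and df2 = (N − 2)(m − 1). The number of measurements m, the correlation ρ and the sphericity value ε are not stated. Assume ρ = 0.5 and ε = 1. With m = 3, λ = 0.04 × 66 × 3/0.5 = 15.84 and power is 0.9504, which reproduces 66. With m = 2 the requirement is 84, and with m = 4 it is 56. But 66 also results from m = 2 at ρ = 0.61, m = 4 at ρ = 0.40–0.41, and m = 5 at ρ = 0.31–0.32. The calculation contains no visit dates and no control type. It cannot decide which schedule or comparator is meant.

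**The case against.** The best defence is that the conflicting sentence is an expectation in an abstract, while the operative rule is in the Statistical analysis section, which is clear about its three points. The immediate assessment agrees in both places, so it would be too much to say that the whole main contrast is contradictory. That limit stands. It does not remove the conflict, because the abstract holds the article's only directional statement about the outcomes and the model as described cannot test its later half.

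A reader might go further in four ways that the article does not support.

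- *That a visit three months after the program cannot fall within the study period.* This needs a session spacing that the article does not give.
- *That 66 participants prove three measurements, so a fourth visit would undo the sizing.* This holds only under an assumed correlation of 0.5, and under that assumption a fourth visit lowers the requirement to 56.
- *That two named comparators allow a favourable one to be picked.* There is one control arm. A wrong label changes what the effect means but offers no second result to choose. Selective choice is plausible for the follow-up time only.
- *That the post-intervention date for e-book controls is undefined, or that the registry entry must change.* The first is detail that a condensed article may leave to the full protocol. The second concerns a record not seen here.

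A friendly reading is that the three months runs from the first session and includes the 4-week follow-up, and that controls get the app afterwards. The first part fits the Methods but not the abstract's wording. The second is stated nowhere. As for standard therapy, the Study design section goes on to describe an e-book or leaflet, so that phrase is a looser label and probably not a third comparator.

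**Conclusion.** The point holds for two items: the later follow-up time and the comparator label. The abstract's assessment three months after the intervention has no counterpart in the planned model, which ends at 4 weeks, and its wait-list has no counterpart in the Methods, where controls receive educational material. The time gap is about threefold (4 against about 13 weeks). No effect on power or sample size is claimed.

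The time conflict is the weightier part, because it leaves the stated follow-up expectation without data and the choice of later time open. The comparator conflict affects how the result is read. The conclusion rests only on the article's own wording and assumes that both follow-up times are counted from the end of the intervention, which is what the abstract says and the ordinary meaning of a follow-up listed after a post-intervention visit. Which schedule was intended cannot be decided from the article.

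**What to change.** 1. Reconcile the abstract's Conclusion, the opening of the Methods, Study design, Recruitment and Statistical analysis to a single visit schedule that is identical in both arms.
2. State which post-baseline time is the primary group × time contrast, before outcome data are examined.
3. If a three-month visit is already made, add it as a time level in the GEE. If it is not, remove the three-month claim from the abstract.
4. Describe the comparator in one way throughout, as what the control group actually receives. Drop the wait-list label unless controls are given the app later, and if they are, say when.

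The cost is wording, with no extra participants. Adding a three-month visit that is not now made would cost an additional round of data collection; the fix does not require it.

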### Sample size

The sample size was determined using the software Based on an a priori power
analysis (G*Power 3.1) ( Faul et al., 2007). An *F*-test (ANOVA: repeated
measures, within-between interaction) was selected as the statistical test,
assuming two groups (intervention and control). The analysis used a conventional
alpha level (α) of 0.05, a statistical power (1 - β) of 0.95, and
a small to medium effect size (f = 0.20), in line with guideline from ( Chow et al., 2002). Based on the
parameters, the minimum required sample size was calculated to be 66
participants (33 per group).

 To account for potential attrition, a 20% dropout rate was anticipated, as
supported by previous studies ( In et al., 2020; Suresh & Chandrashekara, 2012). The adjustment led to an additional 7 participants per group,
resulting in a final target sample size of 40 participants per group, or total
of 80 deaf participants for this study. The final analysis will be conducted
using Generalized Estimating Equations (GEE) to account for the correlated
nature of repeated measures over time and provide robust estimates of
intervention effects.

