### Questionnaire to be utilized in this study

Researchers use Kessler Psychological Distress Scale (K10) from Kessler et al., (2002), is a 10-item
questionnaire assessing anxiety and depressive symptoms over the past four
weeks, with scores ranging from 10 to 50. A score under 20 suggests good mental
health, while scores from 20 to 50 indicate varying levels of mental disorder
severity ( Andrew & Slade, 2001;
Kessler et al., 2002). Coping
self-efficacy questionnaire will be adapting from Chesney et al. (2006), measuring confidence in coping
behaviors, such as problem-focused coping and managing emotions. Respondents
rate their confidence on an 11-point scale, and higher scores indicate greater
coping self-efficacy, with good reliability and predictive validity for
decreased psychological distress and increased well-being. and Knowledge,
attitude, and practice HIV voluntary and counselling testing (K-A-P VCT) from
Addis et al., (2013) is consists of
15 questions assessing participants’ knowledge, attitude, and practice
regarding VCT services. Knowledge is measured through correct answers, attitudes
are evaluated using a 5-item scale, and practice is determined by a single
question about previous use of VCT services.

Questionnaire will be adapting from Addis et al. (2013).

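### For the score outcomes, the analysis section offers only odds ratios and a binary logistic step, although the hypothesis, the instruments and the sample size all concern mean scores

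*Protocol article*

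**What the plan says.** **Instruments** (Questionnaire to be utilized in this study). The K10 covers the past four "weeks, with scores ranging from 10 to 50". Coping self-efficacy is built from 11-point confidence ratings, with higher totals meaning more efficacy. VCT knowledge is a count of correct answers and attitude is a 5-item scale. VCT practice is one question on previous use of the service, so it is binary in effect. A K10 value under 20 is described as good mental health, but it is not defined as an endpoint. No other scale has a cut.

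**Hypothesis** (Abstract, Conclusion). The intervention group is expected to have lower distress scores than the comparison group.

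**Sample size.** The chosen test is introduced with the words "An *F*-test (ANOVA: repeated" and is the form for the interaction of group with time. Alpha is 0.05 and the target power 0.95. The assumed effect, attributed to a published source, is "a small to medium effect size (f = 0.20), in line with guideline from". The result is 66 participants, 33 per group, raised to 80 for dropout.

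**Analysis** (Statistical analysis). As a first step, "the outcome variable was initially examined using binary logistic regression". The primary outcomes (K10, HIV prevention knowledge and practices, and self-efficacy) then go into a GEE with group, time and group × time over three measurement points. The paragraph closes with its only effect measure: "Adjusted odds ratios with 95% confidence intervals are" reported. It gives no family, link, cut-point or mean difference.

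**The concern.** The design and the analysis describe different quantities for the same outcomes. The sample size, the hypothesis and the scales point to a group-by-time difference in mean score. The analysis section points to an odds ratio and a binary model. A GEE for K10 on its own scale cannot produce the effect that the section says will be reported.

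This goes beyond a link function left to a later document, because the article fixes the effect measure. An analysis plan that used mean differences would depart from the article. One that followed the article would abandon the basis on which 66 participants were judged enough. If scores were cut, the cuts would also be open for every scale, and the result would depend on where they were placed. Power could fall far below the planned 95%.

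**Working it through.** **1. Inputs from the article.** Two groups (k = 2), α = 0.05, target power 0.95, f = 0.20 and N = 66 before dropout (Sample size); m = 3 measurements (Statistical analysis).

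**Assumptions not in the article.** Correlation between visits ρ = 0.5, no nonsphericity correction, normally distributed scores, and 30–85% of participants above any cut at baseline. The self-efficacy outcome is taken to be the coping scale, the only self-efficacy instrument described.

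**2. The article's own figure.** For the within-between interaction:

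- λ = f² · N · m / (1 − ρ) = 0.04 × 66 × 3 / 0.5 = 15.84
- df1 = (k − 1)(m − 1) = 2
- df2 = (N − k)(m − 1) = 64 × 2 = 128
- Power from the noncentral F = 0.9504. At N = 64 it is 0.944.

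So 66 is the smallest even N that reaches 0.95, and the stated figure is reproduced. It depends on ρ: with m = 3 the required N is 132 at ρ = 0, 92 at 0.3 and 42 at 0.7. This is a calculation for a continuous outcome.

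**3. What f = 0.20 means in SD units.** f² is the average over visits of (half the group difference, centred over time)².

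- Differences 0, d, d: f² = d²/18, so d = √(18 × 0.04) = 0.85 SD at both follow-ups.
- Differences 0, d/2, d: f² = d²/24, so d = √(24 × 0.04) = 0.98 SD at the last visit.

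**4. Power when the same data are analysed both ways.** Trivariate normal scores with these effects were simulated (4,000 trials per cell) and tested with a robust 2-df Wald test of group × time. The scores were kept continuous (identity link) or cut in two (logit link).

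| Analysis | 33 per arm: 0,d,d | 33 per arm: 0,d/2,d | 40 per arm: 0,d,d | 40 per arm: 0,d/2,d |
|---|---|---|---|---|
| Continuous | 0.96 | 0.96 | 0.98 | 0.98 |
| Cut, 30% above at baseline | 0.56 | 0.49 | 0.64 | 0.57 |
| Cut, 50% above | 0.68 | 0.64 | 0.76 | 0.73 |
| Cut, 70% above | 0.61 | 0.62 | 0.70 | 0.71 |
| Cut, 85% above | 0.43 | 0.47 | 0.52 | 0.54 |

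Simulated type I error was about 5–6% for both analyses, slightly liberal and not enough to change the comparison.

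**5. Sample size to restore 95% power if the scores are cut.** Over the same cuts, the total before dropout is 180, 148, 162 and 246 for the pattern 0, d, d, and 214, 158, 164 and 230 for the pattern 0, d/2, d. The range is 148–246, against 66.

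**The case against.** The strongest reply is that the article never says it will dichotomise anything, and that an odds ratio does not require it. A proportional-odds model gives odds ratios on ordered scores, and a count of correct answers can be modelled as binomial with a logit link. This stands. With 33 per arm, ρ = 0.5 and 0.85 SD at both follow-ups, a proportional-odds analysis had about 89% power with 5 ordered categories and 90% with 8 (600 runs each). The heavy loss comes from cutting scores in two, not from odds ratios as such. Even so, the article names a binary model and no ordinal one, and an ordinal odds ratio is still not the mean difference on which the trial was sized.

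Second, one primary outcome suits the stated method. VCT practice is a single question on previous use, and a logit GEE with an odds ratio is appropriate for it. This stands, so the point is limited to the scores. Attitude is not in the analysis section's list of primary outcomes and is affected only if it is analysed.

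Third, the odds-ratio sentence may be loose wording. The Results section promises effect sizes with confidence intervals without tying them to odds ratios, and a link function often sits in an analysis plan. This softens the point but does not remove it, because the analysis section still states one effect measure and it does not fit most of the outcomes it covers.

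A reader might also infer that the initial logistic step selects variables or ignores the repeated measures. The text supports neither. It says only that associations are examined first, and it does not say whether visits are pooled. The main analysis is explicitly a GEE for within-person correlation.

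**Conclusion.** The point holds for K10, coping self-efficacy and VCT knowledge, and for attitude if it is analysed. For these outcomes, the binary logistic step and the odds ratio contradict the score-scale hypothesis and the F-test sizing.

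The consequence for power is conditional. If the scores are dichotomised, power drops from about 96% to roughly 43–68% at 66 evaluable participants. If all 80 were evaluable, it drops from about 98% to about 52–76%. These figures rest on ρ = 0.5, normal scores, an effect of exactly f = 0.20 in one of two patterns, and 30–85% above the cut at baseline. None of these except f comes from the article. Power was well below 95% in every dichotomised case examined.

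A reader might infer that every primary outcome is affected, that the scores must be cut in two, or that the planned power is already lost. The documents support none of these. Practice is binary, no dichotomy is stated, and the loss occurs only if cutting is what is meant.

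**What to change.** In the Statistical analysis section:

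- For K10, coping self-efficacy and VCT knowledge (and attitude if analysed), specify a GEE with identity link, or a linear mixed model, with group, time and group × time. Report the between-group difference in mean change from baseline with a 95% CI at each follow-up.
- Restrict the logit link and the adjusted odds ratio to the single VCT-practice question.
- Remove the initial binary logistic step for the score outcomes, or limit it to the practice question.
- If a categorical view of distress is wanted, show the proportion with K10 below 20 as a secondary description.

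The cost is a change of wording. No new data, participants or procedures are needed, and the continuous analysis keeps the power on which the sample size was based. The change should be made before outcome data are examined, so that neither the effect measure nor any cut can depend on the results.

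### The protocol treats missing-at-random validity as built into GEE; ordinary GEE does not have it, so dropout that depends on earlier scores differently by arm can bias the group-by-time effect

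*Protocol article*

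**What the plan says.** The Statistical analysis section of the protocol article closes with the missing-data rule: "Missing data will be handled under the missing at random (MAR) assumption", continuing "inherent in GEE, and sensitivity analyses will be conducted to assess the" robustness of the findings. No weighting, imputation method or working correlation is named, and the sensitivity analyses are not described.

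The same section says the three primary outcomes (K10, KAP VCT and CSE) "were analyzed using Generalized Estimating Equations (GEE) to" account for repeated measures. The "model included main effects of group and time, as well as their interaction term", and the comparison is of "control groups across three measurement points (baseline, post-intervention, and" a follow-up visit. On the effect measure it says: "Adjusted odds ratios with 95% confidence intervals are" reported.

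The Sample size section also names GEE as the final analysis and adds: "To account for potential attrition, a 20% dropout rate was anticipated, as" supported by earlier studies.

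**The concern.** GEE in its usual form solves unweighted estimating equations on whatever data are observed. Those equations are in general unbiased only if data are missing completely at random (MCAR), or if missingness depends only on covariates in the mean model. Missing at random (MAR) is wider: it lets dropout depend on earlier observed outcomes, for example a participant leaving because of the K10 score at the second visit. Ordinary GEE does not in general cover that case. Validity under MAR comes from likelihood-based models, multiple imputation or weighted GEE.

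The sentence is therefore wrong about the chosen method, which is different from leaving a detail to a later document. It also presents the problem as solved, which removes the reason to add the device that would solve it. What is at stake is the group-by-time coefficient. If score-related dropout works differently in the two arms, the final-visit means shift by different amounts and the difference enters that coefficient.

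**Working it through.** **The plan's own figures.** The Sample size section gives 66 participants for f = 0.20, alpha 0.05, power 0.95 and two groups. The protocol states neither the correlation nor the sphericity correction. Assuming three visits, correlation 0.5 and no correction, λ = f²·N·m/(1−ρ) = 0.04 × 66 × 3/0.5 = 15.84 on (2, 128) df. Power is 0.9504, and N = 64 gives 0.944, so 66 reproduces. The allowance is 33 × 1.2 = 39.6, hence 40 per group. Only the 20% dropout figure matters for what follows.

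**Inputs.** From the protocol: three visits, group-by-time as the effect, 20% dropout. Assumed here: all loss occurs at the last visit, 20% in each arm; dropout is logistic in the standardised second-visit score z; SD is 7 where K10 units are used; correlation is 0.5 or 0.6; the model has no further covariates.

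**Closed form, Gaussian GEE with independence working correlation.** The group-by-time coefficient is the between-arm difference in observed mean change. Within an arm, the bias at the last visit is ρ × SD × E[z | retained], with E[z | retained] = ∫ z{1 − p(z)}φ(z)dz / 0.8, p(z) = expit(c + bz), and c set so that 20% drop out.

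| Odds ratio of dropout per SD | c | E[z given retained] | Bias, one arm only (ρ = 0.5) | Bias, opposite directions (ρ = 0.5) |
|---|---|---|---|---|
| 1.5 | −1.434 | −0.079 | 0.04 SD | 0.08 SD |
| 2 | −1.521 | −0.129 | 0.06 SD | 0.13 SD |
| 4.5 (b = 1.5) | −1.916 | −0.227 | 0.11 SD | 0.23 SD |

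Bias is given in absolute size. With the same mechanism in both arms the two shifts cancel and the bias is 0. With ρ = 0.6 the last row becomes 0.136 and 0.272 SD. On K10 with SD 7 and a true interaction of −3.00, that is −3.00 − 7 × 0.136 = −3.95 and −3.00 − 7 × 0.272 = −4.90.

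**Simulation with the same inputs** (ρ = 0.6, b = 1.5, ten runs of 100,000 per arm; binary outcome K10 of 20 or more, logit link):

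| Dropout mechanism | K10, independence GEE | K10, weighted GEE | Log OR, full data | Log OR, independence GEE | Log OR, weighted GEE |
|---|---|---|---|---|---|
| MCAR | −2.99 | −3.00 | −0.71 | −0.71 | −0.71 |
| Same in both arms | −3.01 | −3.01 | −0.71 | −0.73 | −0.71 |
| Intervention arm only | −3.95 | −3.00 | −0.71 | −0.92 | −0.71 |
| Opposite directions | −4.90 | −2.99 | −0.71 | −1.20 | −0.71 |

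The simulation matches the closed form. Inverse-probability weighting recovers the full-data value in every row.

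**Exchangeable working correlation, true correlation exchangeable** (single runs of 20,000 per arm, K10 standard error about 0.07). K10 is −2.93 for one arm only and −2.96 for opposite directions, which is within simulation noise of −3.00. The log odds ratio still shifts: −0.74 against −0.68 in full data for one arm only, and −0.83 against −0.69 for opposite directions.

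**A separate simulation with no true effect** (b = ±1.5, opposite by arm, about 20% lost, compound-symmetric then autoregressive data). Independence Gaussian gives 0.240 and 0.296 SD; exchangeable Gaussian 0.014 and 0.013 SD; independence logit 0.364 and 0.369; exchangeable logit 0.121 and 0.192 log-odds.

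**Scale.** With 33 per arm and ρ = 0.5, the variance of a change is 2(1 − 0.5)SD² = SD², so the standard error of the between-arm difference in change is √(2/33) = 0.25 SD.

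**The case against.** The case for leaving the plan alone is about size, and much of it stands.

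- **The large figures need an extreme mechanism.** They need a dropout odds ratio of about 4.5 per SD acting in opposite directions by arm, and nothing in the protocol suggests that pattern. Moderate mechanisms give 0.04 to 0.13 SD, well below the standard error of 0.25 SD. A shared mechanism gives about zero.
- **They also need an independence working correlation.** The protocol does not state one, and an article may leave that choice to the analysis plan. Gaussian GEE of the scores with a well-specified correlation is nearly unbiased.
- **The logit figures for K10 are an illustration.** The protocol reports odds ratios but never says that K10 or CSE is dichotomised. The score of 20 appears under the questionnaires as an interpretation, not as an analysis cut-off. Only the VCT practice question is plainly binary.

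A reader might infer that retention support is unequal because app notifications reach only the app arm. The Recruitment section does not say so. It lists app-based notifications with a WhatsApp group for enrolled participants and periodic check-ins, without separating the arms. Unequal support would in any case point first to unequal dropout rates, whereas this bias needs score-dependent dropout that differs by arm.

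None of this makes the sentence true. The promised sensitivity analyses do not repair it either, because they name no method and no departure from the assumption.

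**Conclusion.** The point holds as a wrong statement about the method the trial relies on. Ordinary GEE does not carry MAR validity, and nothing else in the protocol supplies it. Confidence is high for that statement and lower for the size of any damage.

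The bias in the group-by-time effect ranges from about 0 to about 0.3 SD under the assumptions listed. The top of the range needs an independence working correlation with strong, opposite mechanisms. With an exchangeable correlation and a logit link, roughly 0.1 to 0.2 log-odds remained under opposite mechanisms.

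Two stronger readings are tempting. One is that the 20% dropout will bias this trial by around 0.3 SD. The protocol gives no dropout mechanism, so it supports only that bias is possible. A common mechanism cannot be taken for granted either, since allocation is non-randomised and one arm uses an 11-session app while the other gets an e-book. The other is that GEE must be abandoned. It need not be, since weighting recovered the full-data effect in every case tested. This should be fixed, but it does not threaten the trial's validity on its own.

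**What to change.** 1. Remove the claim that the MAR assumption is inherent in GEE. State instead that ordinary GEE assumes MCAR or missingness that depends only on covariates in the model.
2. Keep GEE as the analysis and add one device that makes it valid under MAR: inverse-probability-of-dropout weights, or multiple imputation by arm, in either case using baseline and earlier scores. For the continuous scores a likelihood-based mixed model is an acceptable alternative, but it is not required.
3. Direct the sensitivity analyses already promised at departures from MAR.

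The cost is a change of wording, a little programming and slightly wider intervals. Sample size and trial conduct do not change. Make the change before outcome data are analysed, so that the choice of method cannot be seen as driven by the results.
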